### Recruitment

Older adults residing in a selected elderly care institution will be screened using the Mini Nutrition Assessment tool (MNA). Older adults who have been identified with a MNA score equal to or less than 11 and satisfied all the other eligibility criteria mentioned above, will be informed about the study both verbally and in writing, in their native language. Information provided will include the aims of the study, participants’ responsibilities, follow-up visits and procedures, potential individual and societal benefits, risks involved, and the ability to withdraw from the study at any time, without any consequences. In addition, opportunities will be provided during this process for any clarification required by the study participants to ensure maximal understanding. Interested participants will be recruited voluntarily. After the written informed consent has been obtained by the co-investigator (PW), participants will be randomly assigned to receive either the oral nutrition supplement or the placebo for 12 weeks.

## Assignment of intervention: allocation

### Sequence generation

Eligible participants will be randomized to intervention and control groups equally (allocation ratio, 1:1) using a simple random sampling technique. The randomization assignment will be generated by one independent investigator (PR) using an online random number generation program.

### Concealment mechanism

Sealed opaque envelopes, indicating the allocation of each participant in accordance with the recruitment number, will be prepared in advance. The researcher who will enroll the participants will be given envelopes displaying the allocation at the time of recruitment. Then, a special participant recruitment number will be assigned to each participant for those who meet inclusion and exclusion criteria and give informed consent in chronological order. The sealed envelope containing the allocation for the given recruitment number is opened, and the corresponding participant will be assigned either into the intervention or control group.

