## Methods: participants, intervention and outcomes

### Study setting

The proposed study will be conducted as an open-label, randomized controlled clinical trial, at a selected residential care facility registered in the National Secretariat for Elders in Colombo, Sri Lanka. Two parallel study groups will include a treatment group and a control group in the same study setting. The study will start with a screening visit to check eligibility.

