### Implementation

Eligible participants will be informed of their randomized assignment once everyone has completed the screening and baseline assessments. The allocation sequence for assigning participants according to the corresponding randomly generated numbers will be produced by a member of the study team (PR) who is not involved in participant recruitment.

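### The concealment text contradicts itself: envelopes described as sealed and opaque are also said to reach the enrolling researcher showing the allocation, before recruitment numbers are assigned

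*Protocol article*

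**What the plan says.** The Concealment mechanism section of the protocol article sets out four steps in this order.

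1. "Sealed opaque envelopes, indicating the allocation of each participant in accordance with the recruitment number, will be prepared in advance".
2. "The researcher who will enroll the participants will be given envelopes displaying the allocation at the time of recruitment".
3. Numbers are then given out by date of entry: "Then, a special participant recruitment number will be assigned to each participant for those who meet inclusion and exclusion criteria and give informed consent".
4. "The sealed envelope containing the allocation for the given recruitment number is opened", and the participant goes to the arm it names.

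The Implementation section adds that the sequence comes from a team member "who is not involved in participant recruitment". It also says that "Eligible participants will be informed of their randomized assignment once everyone has completed the screening and baseline assessments". The Study setting section states the design: "The proposed study will be conducted as an open-label, randomized controlled clinical trial, at a selected residential care facility". Under Who will be blinded, outcome assessors and data analysts are to be blinded. The Discussion says that neither participants nor investigators can be.

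**The concern.** Allocation concealment requires that whoever decides whether and when a person enters the trial cannot foresee that person's arm. An independent sequence generator protects this only while the sequence stays hidden until entry is irreversible. Step 2 puts the envelopes with the enroller, describes them as showing the allocation, and comes before the number that ties an envelope to a participant.

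If staff followed that sentence as written, the enroller could see the next arm and then influence which eligible resident is consented and numbered next. The primary outcome is the proportion gaining at least 5% of body weight, so placing likelier gainers in the supplement arm would favour it whatever the supplement does. Blinding the assessors who weigh participants at 12 weeks does not undo selection that took place before allocation.

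**Working it through.** **Reading the steps against each other**

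| Question | Supports concealment | Works against it |
|---|---|---|
| Can the arm be read before opening? | Steps 1 and 4: sealed, opaque, and the allocation is contained inside | Step 2: the envelopes display the allocation |
| Who holds the envelopes before opening? | No independent holder is stated | Step 2: the enrolling researcher |
| When is the number fixed? | Step 3: after eligibility and consent, in chronological order | Step 3 follows step 2, so the envelopes are handed over first |
| Who assigns the number and opens the envelope? | Not stated (passive wording) | Not stated |
| Who makes the list? | Implementation: someone outside recruitment | – |
| Who learns the arm late? | Implementation: participants, after all baselines are done | Says nothing about what the enroller sees |

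- **First row:** this is a plain contradiction. An envelope cannot be opaque and sealed and also show its contents.
- **Second row:** this does not depend on the word *displaying*. Even with every envelope properly sealed, the separation between list-maker and recruiter ends when the envelopes pass to the recruiter.
- **Third row:** chronological numbering protects the order only if the enroller cannot see the next arm, because the order of consent decides which envelope a resident gets.

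**Illustration of possible size**

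The plan gives no figure for this. The only input from the plan is the 30% responder proportion in the control group (Sample size), applied here to both arms so that the true difference is 0. Three inputs are assumed: the enroller picks between the next two eligible residents, guesses correctly with probability 0.7 whether each will gain 5%, and does so in a fraction f of assignments.

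- P(guessed gainer) = 0.3 × 0.7 + 0.7 × 0.3 = 0.42, so P(guessed non-gainer) = 0.58.
- P(gains | guessed gainer) = 0.21 / 0.42 = 0.50.
- P(gains | guessed non-gainer) = 0.09 / 0.58 = 0.155.
- Steered supplement place: at least one of the two is a guessed gainer with probability 1 − 0.58² = 0.6636. The response rate is 0.6636 × 0.50 + 0.3364 × 0.155 = 0.384.
- Steered control place: at least one of the two is a guessed non-gainer with probability 1 − 0.42² = 0.8236. The response rate is 0.8236 × 0.155 + 0.1764 × 0.50 = 0.216.
- False difference if every assignment is steered: 0.384 − 0.216 = 0.168.

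| Fraction steered, f | False difference (f × 0.168) |
|---|---|
| 0 | 0 |
| 0.25 | 0.042, about 4 points |
| 0.50 | 0.084, about 8 points |
| 1.00 | 0.168, about 17 points |

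Simulation of the same set-up with 25 per arm gave 0.00, 0.04, 0.08 and 0.17. Returning the passed-over resident to the queue gave 4, 9 and 17 points for the three non-zero rows. For scale, the planned difference is 0.75 − 0.30 = 45 points.

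**The case against.** The best defence is the section read as a whole. It calls the envelopes sealed twice and says once that they contain the allocation, against a single use of *displaying*. Opening comes after eligibility, consent and numbering. Step 1 says that the sealed opaque envelopes are *indicating* the allocation, which suggests loose English throughout. On that reading the next arm cannot be seen. In addition, being given envelopes at the time of recruitment may mean one envelope as each participant is recruited, not the whole stock. This defence stands to the extent that the benign reading is plausible.

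A reader might go further and infer that the next assignment is known to the enroller, that the benefit of an independent sequence is lost, or that undetectable bias follows. The documents do not support this:

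- No one is named as assigning the number or opening the envelope, so it cannot be said that the recruiting side controls both.
- Nothing says that the enroller can tell who will gain weight. Screening on the Mini Nutritional Assessment does not establish such foresight.
- Reliance on a single home is unsafe. The retention section speaks of four institutions.
- Baseline weight, body composition, blood tests and diet are recorded. Steering on measured characteristics could show up as imbalance and be partly adjusted for, though not reliably.

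The defence does not remove the contradiction, and it does not answer the custody point. Telling participants their arm late limits what participants know, not what the enroller sees.

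**Conclusion.** The point holds as an internal inconsistency in the concealment procedure, together with a weak custody arrangement. It is not a demonstration that concealment failed. Two findings rest on the text alone: the envelopes are described in incompatible ways, and they are placed with the enrolling researcher before numbers are assigned in an open-label trial. That the enroller could know the next arm holds only on the literal reading.

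The range of about 4 to 17 percentage points shows what deliberate steering could do under assumed steering and guessing rates. It is not an expected effect and should not be quoted as one. Confidence is medium, because one word carries the literal reading. The change is still worth making: the section exists to tell staff what the enroller may see, and it gives two answers.

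**What to change.** Rewrite the Concealment mechanism section so that:

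- the word *displaying* goes, and the envelopes are described as sealed, opaque and sequentially numbered, with only the recruitment number visible outside;
- the independent investigator who generated the list holds them;
- each envelope is released and opened only after the eligible, consented participant has been irrevocably logged against the next number.

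The rewording alone would remove the contradiction. Independent custody goes further, because it carries the separation already promised in the Implementation section through to the point of use.

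The cost is one short contact per participant (50 in all) with someone already on the team, a brief wait for each assignment, and the ethics committee approval that the protocol requires for any amendment.

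The Trial status section reports that recruitment began in February 2023. The investigators should therefore also document how envelopes were held, numbered and opened for participants already allocated, and record the date from which the revised procedure applies.

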### Implementation

Eligible participants will be informed of their randomized assignment once everyone has completed the screening and baseline assessments. The allocation sequence for assigning participants according to the corresponding randomly generated numbers will be produced by a member of the study team (PR) who is not involved in participant recruitment.

## Assignment of intervention: blinding

### Who will be blinded?

The outcome assessors and data analysts will be blinded to the intervention assignment.

### Procedure for unblinding if needed

Participants will not be blinded, given the nature of the study intervention. Single blinding of the outcome assessors and data analysts will be maintained throughout the study.

## Data collection and management

### Plans for assessment and collection of outcomes

The research team will provide sufficient training to the data collectors in order to minimize intra- and inter-observer variations. This includes being familiarized with the research questionnaire and data collection instruments, as well as receiving training on the usage of equipment and measurement techniques. A pre-test will be undertaken using a small group and data will be collected by a well-trained team of data collectors.

Except for DXA scanning and blood investigations, all other tests/measurements will be completed in the study setting. Blood investigations and DXA scans will be undertaken in the Nawaloka Hospitals Laboratory and Radiology department at the Nawaloka Hospitals PLC, Colombo, Sri Lanka. Permission to transport participants to the Nawaloka Hospitals PLC will be obtained from the elderly care institution and National Secretariat for Elders, with participants transported under the supervision of care givers from the elderly care institution.

### Mini nutritional assessment

The MNA short form includes 6 items divided into four areas: anthropometric measurements, global assessments related to lifestyle, dietary questions, and subjective assessment of health and nutrition. The MNA score indicates three different levels of nutritional status: well-nourished (12–14 points), risk for malnutrition (8–11 pints), and under-nourished (< 0–7 points) [24]. MNA will be measured on all residents in both groups, at baseline and after 12 weeks.

### Demographic and medical information

An interviewer-administered semi-structured questionnaire will be used to gather details regarding the participant’s age, and period of stay in the elders’ home. Details related to existing co-morbidities and current medications will be gathered from participants and perusal of their existing medical records.

### Anthropometric measurements

Anthropometric and body composition measurements will be taken by trained data collectors using calibrated equipment according to international recommendations.

Weight: body weight will be measured using the calibrated scale (Seca 813, Hamburg, Germany), to the nearest 0.1 kg using a digital weighing scale with participants wearing light clothing.Height: Height will be taken to the nearest 0.1 cm, as the maximum distance to the uppermost position on the head from heels, with the individual standing barefoot and following full inspiration using a stadiometer (Seca 213 portable stadiometer).BMI: Based on the values of weight and height, BMI will be calculated.Mid-upper arm circumference (MUAC): The midpoint between the acromion and the olecranon process in the non-dominant arm will be marked when the right elbow is 90° flexed placing the forearm palm down across the trunk. The measurement will be taken using a plastic flexible tape (Seca 201, Germany) to the nearest 0.1 cm when the arm is extended alongside the body with the palm facing upwards.Calf circumference (CC): The largest circumference of the calf of the non-dominant leg will be measured using a plastic flexible tape (Seca 201, Germany) to the nearest 0.1 cm in a seated/supine position when the knee and hip are 90° flexed in the two lower limbs.

### Body composition measurements

Skin fold thickness: Assessed using a Harpenden skin fold caliper (British Indicators, West Sussex, UK) at the triceps skin fold site. All measurements will be taken to the nearest 0.1 mm by the same investigator to maintain consistency and inter-rater reliability. Each skin fold measurement will be taken three times on the non-dominant side and the mean value of the three readings recorded following the standard ISAK protocols. Triceps skinfold measurement will be taken parallel to the long axis of the arm at the triceps skinfold site, the point on the posterior surface of the arm, in the mid-line, at the level of the marked mid-acromial-radial landmark. This point is located by projecting the mid-acromial-radial site perpendicularly to the long axis of the arm around to the back of the arm, and intersecting the projected line with a vertical line in the middle of the arm when viewed from behind. The participant will stand with the arm hanging by the side in the mid-prone position and the elbow extended by the side of the body.Dual-energy X-ray absorptiometry (DXA): To estimate fat mass and fat-free mass, DXA measurements will be made with a total body scan (QDR 4500A, fan-beam densitometer, software version 8.21; Hologic, Waltham, USA) that measures the attenuation of X-rays pulsed between 70 and 140 kV synchronously with the line frequency for each pixel of the scanned image. The body scans are to be carried out at an accredited radiography unit.

### Biochemical tests

All biochemical parameters will be tested out at an accredited laboratory (Nawaloka Metropolis laboratory, Nawaloka Hospital PLC) following the standard procedures.

Full blood count: This will be analyzed using SYSMEX XE-2100 Haematology Automated Analyser.HS-CRP: The Roche Cobas c501, which is an in vitro diagnostic test system, will be used to quantitatively determine the C reactive protein (CRP) in human capillary whole blood and serum, EDTA K2/K3 and lithium heparin anticoagulated whole blood and plasma by photometric measurement.Serum vitamin D3: The serum will be separated from the 5.0-mL venous blood sample collected and tested within 3 h using MAGMLUMI 2000 analyzer by Competitive Chemiluminescence Immunoassay (CLIA). This test quantitatively measures the sum of both 25-(OH) vitamin D3 (cholecalciferol) and 25-(OH) vitamin D2 (Ergocalciferol) in the specimen.

### Frailty

The presence of 3 positive indicators of the five fried model indicators: weight loss, exhaustion, low energy expenditure, slowness, and weakness will be considered as frail.

Weight loss: Unintentional weight loss of 4.5 kg or more in the past 6 months and/or BMI of less than 18.5 kg/m^2^ at the time of measurement.Exhaustion: a little or none of the time responses for the Short Form 12-item Survey (SF-12) question, “how much of the time during the past 4 weeks did you have a lot of energy?”.Low energy expenditure: A score < 73 on the Physical Activity Score for the Elderly (PASE) questionnaire.Slowness: The average of two readings in the 6m gait speed test and a gait speed of 0.65 ms^−1^ would be considered “slowness.”Weakness: Hand grip strength < 25 kg would be considered “weak.”

### Peak expiratory flow rate (PEFR)

The PEFR will be recorded using the mini-Wright’s peak flow meter and the value will be obtained in L/min. Three readings will be taken at a time from each participant and the best among these is taken as the final value [26].

### Blood pressure

The blood pressure of the participants will be measured after 5 min of rest, with the back supported and the legs uncrossed. Constrictive clothes will be removed from the upper arm, and the arm will be rested on a table at the chest level. Blood pressure will generally be recorded to the nearest 2 mmHg using digital blood pressure monitors (Omron Healthcare, Singapore). Three blood pressure values will be collected using standard manometers and the average of those values will be considered the final blood pressure value.

### Dietary assessment

A 24-h dietary recall will be taken to assess the dietary pattern of the residents by a dietitian at baseline, follow-up, and endpoint. Food portion sizes will be obtained using standard household measures such as plates, bowls, cups, glasses, and different spoons. The energy content of each food component will be calculated using standard energy values for the portion sizes. The daily energy intakes are to be calculated using NutriSurvey 2000 software. Furthermore, it will be analyzed for macro and micronutrients using NutriSurvey Software modified with Sri Lankan food composition data.

### Physical assessment

Physical Activity Scale for Elderly: Assessment of physical activity will be done using the Physical Activity Scale for the Elderly (PASE), which is validated as a suitable tool to assess the physical activity of the elderly in community studies [27].

### Cognitive assessment

The Montreal Cognitive Assessment (MoCA) is an internationally accepted, widely used instrument for the assessment of mild cognitive impairment, which has been validated for the Sri Lankan population and it takes about 10–15 min to complete [28]. Cognitive domains such as attention, concentration, memory, executive functions, visuo-constructional skills, calculations, orientation, and conceptual thinking can be assessed separately using MoCA. The MoCA score ranges between 0 and 30 a score of 24 or above will be considered normal and a score below 24 will be categorized as mild cognitive impairment.

#### Plans to promote participant retention and complete follow-up

Investigators will phone the managers and caregivers of the four elderly care institutions to remind participants regarding follow-up before each study visit.

#### Data management

Data will be collected and recorded by a well-trained team of data collectors. Any data collected as part of this research project will be stored in a locked filing cabinet at the Health and Wellness Unit, Faculty of Medicine, University of Colombo, for 5 years, under the supervision of the principal investigator (RJ). The data will be stored in a de-identifiable format. Simultaneously, softcopies will be kept password-protected for the above-prescribed period. Following the completion of the due period, the documents will be shredded and the softcopies will be permanently deleted.

#### Patient public involvement

We aim to ensure that our study is patient-centered and addresses the needs and preferences of the target population. To foster active patient involvement, we have established a patient advisory group (PAG) consisting of caregivers and some other older adults caring for older adults with malnutrition and living in the same elderly care setting. The PAG provided valuable insights regarding the acceptability and feasibility of the oral nutritional supplement intervention. Their involvement included collaboration on participant recruitment strategies, considering their life experiences and recommendations for effective outreach. Further, their contribution involved reviewing and providing feedback on study materials including informed consent forms and questionnaires to ensure they were clear, comprehensive, and patient-friendly. The PAG members will meet regularly throughout the study to maintain ongoing engagement.

#### Confidentiality

The data sheets and electronic data files will not contain any personal information. Each participant will be given a unique study code. The document containing the information on the study code and the identity of the patient will be kept separate from the study data files and data sheets.

#### Plans for collection, laboratory evaluation, and storage of biological specimens for genetic or molecular analysis in this trial/future use

None of the blood samples will be utilized for any other purpose outside the intended tests, and no genetic or molecular analysis will be done. Blood samples will not be given to external bodies and sent abroad. All blood samples will be stored for a month to allow for the completion of the tests and safely destroyed.

